## Abstract

Despite the widespread prevalence of mental health problems, most psychological distress remains untreated. Internet-based psychological interventions can be an essential tool for increasing treatment availability and accessibility. The main objective of the MindBlooming project is to design and implement an innovative Internet-based multi-approach treatment for university students suffering from psychological or physical problems. The intervention will focus on symptoms of depression, anxiety, sleep problems, self-destructive thoughts, job- and study-related stress and burnout, and chronic pain. It will be based on different approaches, primarily psychoeducation, Cognitive-Behavioral Treatment (CBT), and third-wave CBT. At the end of the treatment, user satisfaction and usability will be assessed. In addition, two further aims will be evaluating the treatment efficacy through a randomized controlled trial and tuning a predictive model through Machine Learning techniques. The intervention consists of a 7-week treatment on two problematic areas according to each students’ personal needs, identified through an initial assessment. Besides the treatment assigned following the initial screening, participants will also be assigned to a different module to improve their relational skills. The treatment, which can be accessed through a mobile app, consists of psychoeducational videos followed by related exercises. We expect MindBlooming to be a remarkable tool for promoting the mental health of university students.

## 1. Introduction

Worldwide, data about the prevalence of mental health issues are alarming: in 2020, during the COVID-19 pandemic, more than 30% of the general population suffered from depression, anxiety, distress, or insomnia [1]. University students appeared to be highly vulnerable to the risk of mental health deterioration during this period [2]. Specifically, in Italy, between 2019 and 2021, 14% of university students had at least one mental disorder [1]. Young adulthood is a critical phase during which the first psychological symptoms may appear, triggered by the stress related to the university studies and to the new responsibilities of adulthood [2,3]. The prevalence of psychological issues among university students, including depression, anxiety [4], insomnia [5], suicidal thoughts and behaviors [6], stress or burnout [7], and chronic pain [8], appears to be increasing worldwide [5,9]. Mental well-being is connected to our emotionality [10], which is why social isolation and loneliness have a substantial impact on mental health outcomes [11,12] and emotional regulation difficulties represent a risk factor for mental disorders [13]. Furthermore, psychological distress in university students is often associated with a higher risk of failure and dropout from the course of studies [14].

Despite the psychological problems’ high prevalence and significant negative consequences (linked to disability, severe socio-economic issues, and even death), only a minority of university students can access proper treatment [15]. Consequently, promoting university students’ well-being should be a priority of the educational and social systems [16].

Internet-based interventions (IBIs) are a promising way to improve treatment accessibility and availability [17]. These entail the technological implementation of therapeutic treatments that occur in different ways: through web-based platforms, via mobile applications, virtual reality, video games, or feedback and reinforcement interventions through notifications and nudges [15]. IBIs overcome numerous limitations of more traditional forms of treatment related to costs, waiting lists, time and space limits, and the stigma associated with psychotherapy [18]. Several studies reported the effectiveness of self-help IBIs for different issues (i.e., depression, anxiety, sleep-related problems, and chronic pain) compared to control groups [15]. Comparable effectiveness to traditional face-to-face treatments has been observed [19,20]. To date, no risks or negative effects of IBIs have been highlighted [21]. IBIs appear to be a promising tool for university students because, among them, the use of the Internet and smartphones is widespread [22].

MindBlooming is a mobile app for a multi-approach treatment of psychological and physical problems in university students. It represents an attempt to respond to the growing psychological distress of the university population through an easily accessible and always available treatment. The name “MindBlooming” was chosen to evoke the idea of “mental growth”, framing one’s mind as a plant that needs to be cared for. Similar studies have already been performed worldwide [23,24,25,26] but most of them are based on a single intervention approach and face only one or two mental problems. MindBlooming offers a multi-approach and transdiagnostic treatment that allows users to work on different issues through the same app, reducing the commitment needed to use various applications for comorbid issues and therefore increasing treatment efficacy [27]. To the best of our knowledge, this will be the first attempt to deliver such an intervention (i.e., a multi-approach IBI that deals with different psychological and physical problems, and is tailored) to the university students’ population.

### Aims and Hypotheses

MindBlooming is a two-year research project with multiple primary goals and related hypotheses. Firstly, we aim to design and implement a new Internet-Based Multi-Approach Intervention (IB-MAI) for university students. The intervention covers a wide range of mental health issues that are relevant within the university student population [11,28] and that are treatable with IBIs [23,25,29]. Furthermore, the intervention is tailored to the individual’s needs. The mental health issues that MindBlooming addresses are depression, anxiety, sleep problems, self-disruptive thoughts, job- and study-related stress and burnout, and chronic pain.

Secondary aims will be: (1) the feasibility assessment of this IB-MAI (in terms of acceptability, satisfaction, usability, and uptake) through a pilot study on a restricted sample; (2) a randomized controlled trial (RCT) to compare the IB-MAI with web-education, as the control condition (CC); and (3) exploratory analysis to tune a predictive model on the collected data adopting Machine Learning techniques.

We hypothesize that: (1) the design and implementation of the IB-MAI treatment will be feasible; (2) the majority of the students will accept and be satisfied with the treatment; (3) the IB-MAI will be superior to the CC on both the primary and secondary outcome measures; and (4) the large amount of collected data will allow the identification of predictors of treatment response and different trajectories in treatment response.

## 2. Materials and Methods

The project has already been approved by the Internal Review Board (IRB) of the University of Milan-Bicocca at the beginning of the year 2021 (protocol number: 0018862/21; date: 16 February 2021). The study will be organized into two phases. The first phase, which has already been completed, focuses on the IB-MAI design and implementation. An in-depth analysis of current IBIs was conducted to design the IB-MAI. This allowed us to analyze the strengths and limitations of different approaches and use these observations to guide the development of the intervention. Our IB-MAI was designed as a mobile app for both Android and iOS to increase the number of potential users. MindBlooming provides a set of psychoeducational videos (with transcripts) about the psychological issues faced during treatment, as well as questionnaires and exercises to collect information before, during, and after the treatment itself. We followed the design principle of Material Design [30], which is a system of guidelines, components, and tools that support the best practices of user interface design and specify theories and practical applications of the interaction among human and machine for mobile development. The user interface (Figure 1) has been developed following the current usability standards, and it comprises features such as reminders, nudges, a calendar, and a diary.

The second phase will consist of 3 main steps. In the first step, a pilot study will be performed by recruiting 30 participants to evaluate the feasibility of this IB-MAI (acceptability and satisfaction, usability, and uptake). An RCT will be conducted in the second step. The pilot study and the RCT structure will be described in detail in the following paragraphs. Lastly, data analysis will be performed through Machine Learning techniques.

### 2.1. Participants and Recruitment

University students aged between 18 and 29 will be invited to participate; to be included, they must declare to have experienced at least mild- or moderate-intensity forms of mental health symptoms (no specific diagnostic screening will be performed in this phase), and they must not currently be in psychotherapy or start psychotherapy during the entire duration of the treatment. Participants are also required to have a phone based on Android or iOS operating systems and an Internet connection. Exclusion criteria include the inability to communicate in Italian.

Participants will be recruited through social networks (e.g., Facebook and Instagram), students’ WhatsApp groups (to include students not using the mentioned social networks, thus avoiding selection biases), and the Sona System recruitment platform made available by the University of Milan-Bicocca. Moreover, to further encourage participation, posters will be placed in local universities. In this phase they will receive preliminary information. Then, through a web link, they will be redirected to a specific landing page with more detailed information about the mobile app. On this web page, participants will be redirected to the proper marketplace (Apple Store and Google Play) to download the app on their smartphones. If possible, European Credit Transfer and Accumulation System (ECTS) credits will be awarded to participants. Once their eligibility has been verified and they have signed an online informed consent form, students interested in participating will be included in the study. We will collect the information concerning the diverse participants’ recruitment channels to ensure that there is no difference in baseline data among different recruitment channels. The same standards for data collection will be applied through different channels.

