### 2.3. RCT Design

This study will be conducted in accordance with the Consolidated Standards Of Reporting Trials (CONSORT) checklist for the RCT design [34]. Participants will be randomly assigned following blind simple randomization procedures when they complete the baseline assessment (randomization sequence under computer control adopting computerized random numbers) to 1 of 2 treatment groups (see Figures S1 and S2 for the study design and assessments). We only keep the 1:1 ratio constraint at the 260th participant, meaning that when one group reaches 130 participants, all the remaining volunteers (up to the total of 260) will be allocated to the other group. Students will be randomized to IB-MAI or CC. Participants in the intervention condition will receive an 8-week unguided IB-MAI program, i.e. MindBlooming. Participants in the CC condition will access websites with information about their specific areas of distress identified at baseline. Participants will be assessed with repeated measures (baseline, 8 weeks, 12 weeks, and 24 weeks). The RCT participants’ flow is presented in Figure 2.

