Every week for the entire duration of the intervention, participants will have access to one session per module, except for the 6th week, which is dedicated to the treatment of relational problems: regardless of the specific issue (depression or anxiety, etc.), this training deals with relational issues relevant to everyone, hence the importance of transversally proposing it. The modules will be presented as follows:○1st week: module 1 and 2 sessions;○2nd week: module 1 and 2 sessions;○3rd week: module 1 and 2 sessions;○4th week: module 1 and 2 sessions;○5th week: module 1 and 2 sessions;○6th week: relational problems related to difficulties in emotion regulation and empathy deficits session;○7th week: module 1 and 2 sessions about relapse prevention, future planning by reflecting on how to attain goals and implement behavioral changes, orientation, and conclusion.

All online sessions will include psychoeducational videos (brief seminars of 15 min each, with audios and PowerPoint presentations), about epidemiology, explanatory models, risk and protection factors, treatments, and some specific aspects of each psychological issue. Once the videos have been seen, training exercises will be proposed to help participants to integrate the content of the sessions into their daily lives (Figure 3). Contents and approaches used for each module are further presented in Table 1.

Quizzes will be presented during each session, along with the possibility for the participants to reply and insert text. Subsequent sessions will be available only if the previous session, and a minimum of related exercises, is completed within 7 days (+3 days to be flexible in the case of students unable to maintain the pace). Even if the contents are completed before the 7th day from the start, new contents will be available from the 7th day onwards. When a new week of treatment is available, participants have 3 days to start completing the tasks. If the subjects do not respect the deadlines, they will be excluded from the study. Participants also have access to a list of available supplementary resources.

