For the entire duration of the treatment, participants must answer daily and weekly questions related to each of the two treatment modules they are individually following to constantly monitor the progress of some key variables. The sixth week is an exception, as daily and weekly questions will also address relational issues. Answers are saved and shown to participants on a calendar to follow-up changes over time. Moreover, participants are informed that they can contact an e-Coach for technical questions and concerns or emotional crisis at any time during the intervention.

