### 2.8. Statistical Methods

Statistical analyses will be conducted adopting both a frequentist and a Bayesian approach to provide robust evidence favoring or against the intervention.

The main study outcome is to verify the effectiveness of the intervention: this would be verified by a T0 to T1 delta different from 0. Additionally, we will test the effectiveness of the IB-MAI against the CC group comparing the two T0 to T1 deltas. We will use a series of *t*-tests and its Bayesian [83] corresponding test.

Stability over time will be verified with a mixed ANOVA using the T1, T2 and T3 datapoints as within-subject measures and group (IB-MAI versus CC) as a between-subjects factor. We will use “classic” (i.e., frequentist) ANOVA and its corresponding Bayesian version [84] for each primary and secondary outcome measure.

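### Not starting psychotherapy during treatment is made a condition of inclusion, yet it can only be known after randomisation

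*Protocol article*

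**What the plan says.** Section 2.1 of the protocol article lists what a student must satisfy to be included. The symptom criterion, "at least mild- or moderate-intensity forms of mental health symptoms", is something the student declares. The psychotherapy criterion is a flat condition on conduct: students "they must not currently be in psychotherapy or start psychotherapy during the entire duration of the treatment".

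The same section fixes when eligibility is settled: "Once their eligibility has been verified and they have signed an online informed consent form", the student enters the study. Section 2.3 then states: "Participants will be randomly assigned following blind simple randomization procedures when they complete the baseline assessment". Treatment follows, described as seven weeks in the abstract and section 2.4 and as eight weeks in section 2.3.

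The only removal after randomisation that the article prints is for late sessions in section 2.4: "If the subjects do not respect the deadlines, they will be excluded from the study". It gives no rule for a randomised student who starts psychotherapy.

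In section 2.8, the main study outcome is effectiveness of the intervention, and "this would be verified by a T0 to T1 delta different from 0". The comparison of the two arms' T0 to T1 changes is stated as an addition.

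**The concern.** An eligibility criterion has to be decidable before allocation. The first half of this one is: current psychotherapy can be asked about at T0. The second half is not. Whoever applies the criterion as written finds that a student who was eligible at randomisation becomes ineligible later, because of something that happened under the allocated condition.

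Starting psychotherapy is unlikely to be a neutral event. Students who are doing worse may be more likely to seek it, and the two conditions (an app programme and a list of websites) may lead to different start rates. If starters were taken out, the remaining groups would no longer be the randomised groups. The within-arm change would be affected even if start rates were the same in both arms, because the students removed would tend to be those with the poorer course.

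**Working it through.** **1. Order of events.** From sections 2.1, 2.3 and 2.4: eligibility check and consent, baseline assessment (T0), randomisation, treatment weeks, T1. The psychotherapy clause covers the treatment weeks, which come after both the eligibility check and randomisation. The end of that period is also settled after allocation, since section 2.6 says that treatment duration can differ between students.

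**2. The plan's own figure.** Section 2.7 gives d = 0.40, two-sided alpha 0.05, 80% power, 200 completers and 260 recruited. Per arm, n = 2(1.960 + 0.842)² / 0.40² = 98.1, so 99 per arm and 198 in total, against 200 stated. With the t-test, 99.1 per arm are needed, and power at 100 per arm is 80.4%. Implied attrition is 1 − 200/260 = 23.1%. The sample size reproduces and is not at issue.

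**3. Illustration: precision if starters were removed.** The documents give no start rate; the rates here are assumed. Removing a share q of the 200 completers, equally from both arms:

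| q | remaining | power at d = 0.40 |
|---|---|---|
| 2% | 196 | 79.6% |
| 5% | 190 | 78.3% |
| 10% | 180 | 76.1% |
| 15% | 170 | 73.7% |

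**4. Illustration: selection if starters were removed.** Suppose the share q with the highest propensity to start is removed, and this propensity correlates r with a worse T0 to T1 change. The arm's mean change then shifts in the favourable direction by r·φ(z)/(1 − q), where z is the (1 − q) normal quantile. The multipliers of r are 0.1086 (q = 5%), 0.1950 (10%) and 0.2743 (15%). With r assumed at 0.3 to 0.5:

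- Within one arm: 0.033 to 0.054 SD at 5% starters; 0.059 to 0.098 SD at 10%.
- Between arms, equal q and r: 0.
- Between arms, 5% versus 10%: (0.1950 − 0.1086) × r = 0.026 to 0.043 SD.
- Between arms, 5% versus 15%: (0.2743 − 0.1086) × r = 0.050 to 0.083 SD.

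A simulation with 130 per arm and 20,000 runs agrees: 13 versus 13 removed at r = 0.5 gives 0.000; 6 versus 13 at r = 0.3 gives 0.028; 6 versus 20 at r = 0.5 gives 0.089.

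**5. A second parameterisation.** If starters' change is k SD worse than that of other students, removal shifts the difference by k times the difference in start rates. With 5% versus 15% and k of 0.5 to 1.0, this is 0.10 × k = 0.05 to 0.10 SD.

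**6. Direction.** If more controls start and are removed, the control mean improves and the contrast narrows. If more app users start, it widens. The documents do not say which is likelier.

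**The case against.** The strongest reply is that the harm depends on a rule the article does not contain. A reader might infer from the clause that starters are withdrawn or dropped from the analysis. The text does not support that: removal is printed only for missed deadlines, and the handling of later psychotherapy may stand in a full protocol or analysis plan that is not shown. This stands. The bias is therefore conditional, and the silence about handling is not the point made here.

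A second reply is that the clause is meant as an undertaking given at enrolment. That is a reasonable guess at the intent, but the sentence ties self-declaration only to the symptom criterion. Even an undertaking cannot make later conduct a condition of inclusion. This reply does shape the remedy: deleting the clause outright would admit a student with therapy already arranged, so planned therapy should stay in the criterion.

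Third, every rate and correlation in the illustration is assumed. That also stands.

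Three further inferences should not be drawn:

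- That the period lasts at least 49 days. Section 2.4 opens new content from the seventh day and allows early completion, so the seventh week opens around day 6 × 7 = 42 and may be finished soon after.
- That the Conclusions set an upper severity limit which section 2.1 omits. They describe what the results could contribute to, not who may enter.
- That the clause is shown to deter students in crisis from seeking help. The consent text is not available, and students are told that "they can contact an e-Coach for technical questions and concerns or emotional crisis at any time during the intervention".

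**Conclusion.** The point holds as a defect in what section 2.1 prints: half of an inclusion criterion depends on an event after randomisation, and followed literally it makes a randomised student ineligible. That rests on the order of events alone and needs no assumption.

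The consequence for the results is possible, not stated. It arises only if starters are excluded, and its size and sign cannot be obtained from the documents. Under the assumptions shown it is modest: nothing between arms with equal rates and equal selection, and otherwise some hundredths of an SD against a design effect of 0.40. The within-arm change is the more exposed quantity, because equal start rates do not protect it. The wording is worth correcting because the correction is cheap and closes a route to selection after allocation.

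**What to change.** In section 2.1, replace the psychotherapy clause with: *not in psychotherapy and not planning to start it, as declared at T0*. Add: *Starting psychotherapy after randomisation is not a reason for exclusion in either arm; such students are followed at T1, T2 and T3 and analysed in their allocated group.* Record starts in both arms with one self-report item at T1, T2 and T3 (started since the last assessment, yes or no, and date), and report the counts by arm. The article mentions therapy questions only at T0.

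The cost is a wording change and one item at three existing assessments. There are no new visits, and the sample size does not change.

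The downside is that the estimate then includes some concurrent psychotherapy. If psychotherapy adds 0.3 SD by T1 and 5 to 10 percentage points more controls than app users start it (both assumed), the contrast narrows by 0.3 × 0.05 = 0.015 to 0.3 × 0.10 = 0.030 SD. With 100 per arm, power falls from 80.4% at d = 0.400 to 77.3% at 0.385 or 74.0% at 0.370. On the same 0.3 SD assumption, 5% to 10% starters in the app arm add 0.015 to 0.030 SD of therapy benefit to its within-arm change. The counts by arm would show whether either matters.

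This change covers psychotherapy starts only. The deadline rule in section 2.4 would still remove an app user who falls behind, whether or not that student has started therapy, and needs its own decision.
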